#### *3.1.14. Strengths and Limitations to the study*

- Randomization should ensure that the effect estimates are not biased by known or unknown confounders.
- HIV status might be an important confounding or modifying factor, but HIV status will not be assessed among the participants. The very low expected HIV sero-prevalence in young children in Burkina Faso should not have substantial consequence on the results of the study.
- Selection biases will be kept to a minimum by ensuring allocation concealment. However, rate of withdrawals (including refusals after randomization) and/or loss to follow-up might differ according to the allocated group. High follow-up and defaulters tracing will be ensured in all arms and incentives will be provided to increase the motivation of all participants.
- Observer biases will be kept to a minimum by blinding the staff responsible for the outcome assessments with respect to the allocated group. In addition, all participants and staff involved in the study will be blind to the milk and soy compositions of the iCSBs and LNS supplements.
- The tracer dilution technique might be difficult to conduct in young children. The study staff will receive an appropriate training and benefit from continuous supervision.
- Possible lack of adherence and contamination between groups may be an important limitation of this study. This study will examine the effectiveness of the food supplementation (rather than the efficacy), that is, a combination of biological/nutritional and logistical/practical effects, which is relevant in practice. Hence, childcare practices related to supplementary feeding and the adherence to the food will be assessed (see

section 3.3). The importance of following the nutritional prescription will be stressed during the health and nutrition education provided to all participants.

- A potential limitation of the study is generalizability, as nutritional status is likely to differ between populations.

### 3.2. Child care practices related to supplementary feeding and the perception, acceptability of and adherence to the food

Childcare practices related to supplementary feeding and perceptions, acceptability of and adherence to the foods will be explored by doing structured observational studies, in-depth and semi-structured interviews, questionnaires as well as Focus Group Discussions (FGD).

**Structured Observations** are included in order to gain a realistic picture of actual practices rather than just the informants' views on "correct" perceptions. In this way, this part of the study aims at exploring social activities and the meaning given to these by observing phenomena in their natural setting on a limited subsample.

A trained local assistant will be observing the caretakers and children in the private home of the family during daytime to explore child care practices related to feeding and adherence to treatment and will include observations on particularly:

- *Caregiver's feeding behaviors* such as frequency of and time devoted for supplementary feeding of the child, interaction with the child during feeding incl. level of supervision and encouragement and hygiene behaviors related to the feeding situation (Dearden et al. 2009; Flax et al. 2010)
- *Child feeding practices*, such as the position of the child during the feeding situation, the way the child is fed and utensils used for feeding and how and when the supplementary diets are consumed (i.e. as snacks or as a meal, as individual diets or shared with other household members (Pelto et al. 2003; Flax et al. 2010; Shankar et al. 1998)i
- *Adherence to the treatment* in terms of compliance to treatment and to which degree the products are stored, prepared and distributed according to recommendations.

It is planned for the local assistant to spend three consecutive days (during daytime) in the household of each of the participants. For practical reasons, 20 participants will be randomly selected from one of the recruitment sites (10 participants from the LNS groups, 10 participants from the CSB groups)

Furthermore it is planned to carry out 10 semi-structured interviews and 10 focus group discussions (4-6 participants in each). Caretakers will be randomly selected at the recruitment sites but will consist equally of participants receiving either LNS or CSB products. The interviews and FGDs will be carried out at the recruitment site, in a secluded and quiet area, during the waiting time of the visit at three months. The aim of this part of the study will be to explore perceptions about nutrition, malnutrition, the food products, the treatment as well as the acceptability and perceived benefits and/or undesirable effects of the products. A trained research assistant will conduct/moderate the interview/discussions in local language in a place ensuring privacy. The interview/discussions will be audio recorded for later transcription and translation.

A separate informed consent form will be made for participants agreeing to participate in this part of the study describing the purpose of the study. It will be clearly stated that participation is voluntary and that refusal to participate will not affect the treatment that the child is otherwise receiving or the participation in the main study.

The consent forms will be translated into the local language and read out to the child's caretaker. Each participant will receive a copy of the information sheet and consent form. After giving appropriate time to consider, the caretaker will be asked if he/she wishes to participate in the study and allow the research assistant to visit the household for three consecutive days. If they agree, they will be asked to sign the informed consent form. If the caretaker is illiterate, a thumbprint will be accepted instead of a signature, and in this case, a literate witness is required to sign to confirm that the information material has been read out accurately to the caretaker.

**Questionnaires:** At the first follow-up visit (2 weeks into supplementation) all caretakers of participants in the study will be asked questions on the acceptability of and adherence to the products, following a structured questionnaire. This questionnaire will include questions on the perception of the quantity, appearance, taste, smell and consistency of the products and will be assessed according to a five-point Hedonic scale (from “5” – “like very much” to “1” – “dislike very much”). Furthermore questions regarding the health of the child and breastfeeding patterns during supplementation as well as feeding practices will be asked.

With the assumption that acceptability of new foods increases, if it is served for a longer period of time, the questionnaire will be repeated at the end of the supplementation period (at 3 months). Furthermore caretakers will at this point be asked questions related to food security based on the assumption that foods may be more acceptable in households with high food insecurity. Food security will be assessed using questions from the Household

Food Security Access Scale (HFIAS), and the level of food insecurity for each household will be classified into four levels of food insecurity (food secure, mildly food insecure, moderately food insecure, severely food insecure) (Annex 8). Furthermore a trained research assistant will administer the questionnaire in the local language.

## **4. Ethical and administrative considerations**

### **4.1. Authorizations**

The study protocol has been granted approval from the Ethical committee of Burkina Faso (August 2012, see annex 9) and the Danish National Committee on Biomedical Research Ethics (September 2012, see annex 10). Furthermore the study has received authorisation to import and export study related material from the Direction Générale de la Pharmacie du Médicament et des Laboratoires (DGPML) under the Ministry of Health in Burkina Faso. The study will be conducted in accordance with the principles of the Declaration of Helsinki and international ethical guidelines for biomedical research involving human subjects, published by the Council for International Organizations of Medical Sciences (CIOMS). Prior to the study, community leaders will be informed about the purpose of the study. Authorization for the study will be obtained from the Ministry of Health, Burkina Faso.

### **4.2. Informed Consent**

The consent process will include separate information notices and consent forms for the trial, and for the “practices, perception, acceptability, and adherence” study, (annexes 11, 12 and 13). All documents will be translated into local languages, and back-translated to ensure accuracy. For all children eligible for participation in the trial, the trial information notice will be explained orally to their parents or guardians who will receive a printed copy. After answering any questions about the study, the investigator will ask the parent or caretaker, keen to participate, to sign (or fingerprint if the signature can't be obtained) the trial consent form. Any activities related to the study other than the pre-screening (W/H and MUAC) will only be done after the caretaker or parent has signed the informed consent. Copies of the written informed consent will be given to the parent or caretaker and another copy will be kept at the office of ALIMA in Yako. A literate witness will be required to be present during the reading of the consent form and sign in addition to the fingerprint requested from a non-

---

 Coates J, Swindale A & Bilinsky P (2007) Household Food Insecurity Access Scale (HFIAS) for Measurement of Food Access: Indicator Guide. Food and Nutrition Technical Assistance Project (FANTA)

literate study participant. The same procedure will be followed for the caretakers invited to participate in the pilot study or the “practices, perception, acceptability, and adherence” study, using the appropriate information notice and consent form.

Any personal data (case reports, laboratory records, registers, or other forms, audio and video records) will be kept confidential and will not be disclosed to anyone outside the study teams. The electronic database will not contain names or addresses of patients to ensure their anonymity.

All children recruited in the study in need of medical treatment, will be treated according to National Guidelines. The inclusions in the study will be made voluntarily and refusals to participate in the study will have no influence on the medical treatment provided to the child in the health center. Refusing to participate in the pilot study will not have any influence on the participation in the trial.

#### 4.3. Risks and benefits

There is no major risk associated to this research project.

There are no obvious risks related to the tracer dilution test and no danger related to the deuterium solution. The tracer deuterium is a stable, naturally-occurring isotope. Stable isotopes have been used in human metabolic studies for more than fifty years. Tissue concentrations below 15% have not been associated with harmful effects. Trivial transitory side effects as transitory episodes of vertigo have been reported at concentrations around 0.35-0.65%. However, the amount of tracer consumed in studies of body composition such as this, enrich body water to a maximum of 0.1%. At this level no adverse side effects have been reported (IAEA). However, discomfort may occur during saliva sampling, especially for the youngest children. This procedure requires concentration and focus of the participant, which may be difficult for a small child to uphold. All measures will be made to reduce discomfort as much as possible.

Participants in this study might suffer discomfort related to the blood sampling. To reduce discomfort, an analgesic ointment will be applied to the skin of the child prior to blood sampling. Blood collection may cause localized pains, small hematoma following insertion of the needle, or, rarely, phlebitis. A maximum of 2x2ml of blood will be collected. The amount of blood removed will be too small to affect the child's health. Blood sampling will be attempted in two tries for each child. If not successful, the procedure will be postponed to the next follow-up visit.

Finally, allergic reactions such as rash, vomiting/diarrhoea, respiratory problems or allergic shock within the first hour of eating the food are a potential risk. The first dose of the

products will therefore be eaten under supervision of the study staff and in case of allergic reactions, relevant measures will be taken.

The study will include various benefits for the participants: food distribution, incentives, and nutritional and health education. In addition, each child will benefit from a fortnightly or monthly close clinical follow-up and, if found sick (or severely malnourished), would receive standard therapy following national clinical guidelines.

Finally, the results will help adapt the guidelines for the treatment of MAM in Burkina Faso and will have an essential programmatic effect on the future of ALIMA's nutritional program strategy. If acceptable and cost-effective products were identified for the management of MAM, this would furthermore benefit communities prone to food insecurity and high malnutrition rates.

In addition, this study will also strengthen local research capacities through the training of local research staff members and technicians.

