### 3. Methods

#### 3.1. Effectiveness randomized controlled trial

##### 3.1.1. Study setting and study period

The trial will be conducted in selected district health centers “Centre de Santé et de Promotion Sociale” (CSPS) supported by ALIMA in the province of Passoré in the northern region of Burkina Faso. ALIMA’s program consists of support to district health structures for the management of severe acute malnutrition (SAM) in the District hospital of Yako and 53 CSPS in the province of Passoré. The trial will take place in five selected CSPS. Admission and follow-up take place 5 days a week on each site. The recruitment of children for the trial is expected to begin in August 2013. The intervention is planned for three months, with an additional three months of follow-up.

The prevalence of HIV among adults in Burkina Faso is 1.2 %. The estimated number of HIV infected children among our study participants is therefore likely to be very low.

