##### 3.1.2. Study population

Children will be eligible for inclusion if they fulfill the following criteria:

- weight-for-height z-score (WHZ)  $\geq -3$  and  $< -2$  (based on the WHO growth standard) or
- MUAC  $\geq 115$ mm and  $< 125$  mm
- 6 to 23 months of age,
- resident in the catchment area at the time of inclusion,
- whose parents/guardians have signed (or thumb-printed whenever illiterate) the informed consent.

---

 From 7.30am to 4 pm, all year long.

 UNAIDS 2009

 According to the workload, prior MUAC screening might be implemented.

 A local calendar of events will be piloted. If it does not appear suitable for inclusion based on age, children would be included based on a combination of event calendar and height.

Will be excluded:

- Children with severe acute malnutrition defined as a WHZ < -3, and/or a MUAC <115 mm, and/or bilateral pitting oedema. They will be referred to the health centres or Yako hospital for appropriate treatment,
- Children with medical complications requiring hospitalization,
- Children whose household plans to leave the catchment area in the next 6 months.
- Children with a hemoglobin concentration <4g/dl or with evidence of a decompensate anemia (eg, dyspnea, tachycardia...). These children will be transferred to the ITFC supported by ALIMA for appropriate treatment.
- Children who have been treated for SAM or who have been hospitalized in the last 2 months,
- Children with known allergy to milk, peanut, CSB and/or RUTF,
- Children with a severe disability limiting the possibility of investigations,
- Children enrolled in any other nutritional program or part of any other study conducted in the area.

Children with MAM who do not wish to participate in the study or who are excluded due to some of the above mentioned criteria, will be referred to the national supplementary nutritional program currently supported by WFP.

Appropriate free care, including referral to nutritional rehabilitation or pediatric care at Yako hospital (supported by ALIMA) when needed, will be offered to children who are non-eligible due to SAM or decompensated anemia.

Children will be recruited among children presenting spontaneously at the CSPA. All children taken to CSPA will be screened for eligibility. Furthermore active case finding within the community by community health workers supervised by ALIMA will be done.

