#### *3.1.9. Blinding*

This is an open trial since participants will not be blinded with respect to main type of food (LNS or iCSBs). However, within the arms with either iCSBs or LNS, participants will be blinded to the soy and milk content of the food. The investigator measuring the primary outcome (lean body-mass using tracer dilution) will be kept unaware of the allocation group and will therefore be blinded with respect to main type of food. In addition, the investigators measuring other biological factors, physical activity and milestones development will be blinded with respect to main type of food.

After baseline data have been collected, the child will be referred to the Supplement Responsible (SR). Only the SR will have access to the random sequence list.

For further information on the randomization and management of the experimental products, please see Standard Operating Procedure in annex 6

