### **Child development**

Child development will be assessed in all children at baseline and after 3 and 6 months using a piloted and adapted version of the Malawi Developmental Assessment Tool (MDAT) (Gladstone *et al.*, 2010). The tool will focus on gross and fine motor development as well as language development and includes 30 milestones in each domain. Thus a total of 90 milestones

For the main study, testing of the child will take place in a quiet area. The child should be alert and well enough to be cooperative. If a child is too tired, irritable or sick to cooperate, the test will be postponed to the next fortnightly visit. The test will be carried out by trained health workers, in the presence of the mother/caretaker of the child. Health workers will evaluate each child starting with at least three milestones before the most age-appropriate milestone in each domain. . If the child passes these milestones, prior milestones will be rated as observed passed (10 points), Milestones will be rated with scores 10, 5 or 0. If the child can perform the milestone while being observed, the child will score 10. If the child cannot perform the milestone while being observed, but the mother reports that the child is able to perform the milestone at home, the child will score 5. If the child cannot perform the milestone and the mother reports that the child is not able to do so at home, the child will score 0.

After having failed six consecutive milestones in a domain (gross and fine motor or language), the assistant will move along to the next domain, following the same procedure.

After the evaluation, a total score will be calculated for each domain and an evaluation of the behaviour and cooperation of the child as well as the involvement of the mother will be carried out.

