## **Blood sampling and analyses**

Blood samples will be taken at baseline and thereafter at 3 and 6 months of follow-up. An anesthetic crème will be applied to the skin prior to blood sampling to minimize pain.

2.5 ml of venous blood sample will be collected by standard phlebotomy. Directly after taking the blood sample 1 drop of whole blood will be put on filter paper with BHT – to be dried and stored in 4°C. Furthermore, 1 drop will be used to estimate hemoglobin concentration (HemoCue) on the spot and 1 drop will be used for malaria rapid-test on the spot (local standard).

The rest of the blood will be put into a tube and taken to the lab in Yako. At the lab the blood will be centrifuged and the serum added to small tubes, stored at -20°C and then transported to the labs for analysis.

Since no laboratory in Burkina Faso performs all the desired analyses for research purposes, the samples will be exported for analysis.

- 0,2 ml of serum will be send to University of Copenhagen for analysis of IGF-1.
- 0,2 ml of serum will be sent to Germany for analysis of CRP, AGP, ferritin, Retinol Binding Protein, (RBP) soluble Tranferrin Receptor (STR).

---

 Department of Human Nutrition, [name]

- 1 drop of dry blood on filter paper will be sent to Canada for analysis of essential fatty acid status.

As a precaution, remaining serum will be collected in a tube and will be sent and stored at the University of Copenhagen at -80 degrees C for 5 years in anonymous form. Remaining plasma will be used only to measure other indicators of nutritional status (e.g. Hepcidin), growth and infection related to this study. After 5 years the samples will be destroyed. No analyzes other than the ones mentioned here will be performed.

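### Failed blood draws and development tests move to the next visit with no exception for baseline, month 3 or month 6, so some secondary-outcome values would be mistimed

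*Combined protocol and SAP*

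**What the plan says.** - **Blood.** Section 3.1.11 (Blood sampling and analyses): "Blood samples will be taken at baseline and thereafter at 3 and 6 months of follow-up". Section 4.3 allows two tries per child, then: "If not successful, the procedure will be postponed to the next follow-up visit".
- **Development test.** It is scheduled at the same three time points. For a child too tired, irritable or ill to cooperate, "the test will be postponed to the next fortnightly visit" (section 3.1.11, Child development).
- **Date of the next visit after entry.** Section 3.2, on the acceptability questionnaire: "At the first follow-up visit (2 weeks into supplementation".
- **Order at entry.** Section 3.1.9: "After baseline data have been collected, the child will be referred to the Supplement Responsible (SR". Section 3.1.8 has the envelope opened only once screening and recruitment are complete.
- **Later visits.** Sections 3.1.3 (Medical treatments) and 3.1.11 (Anthropometric measurements) make visits fortnightly during the intervention and monthly during follow-up, ending at month 6.
- **Haemoglobin.** Section 3.1.2 excludes "Children with a hemoglobin concentration <4g/dl or with evidence of a decompensate anemia". The scheduled reading comes from the venous sample: "1 drop will be used to estimate hemoglobin concentration (HemoCue) on the spot". A footnote to Table 2 also allows a HemoCue reading, when needed, within the nurse's examination, which is marked at month 0.
- **Analysis.** Section 3.1.13 does not say how a value obtained late is to be classified.

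**The concern.** Both postponement rules are general, so as written they apply at baseline, month 3 and month 6. At baseline, the next visit comes after the child has started the product. At month 3, it comes after the product has stopped. At month 6, there is none.

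The outcomes at stake are haemoglobin, ferritin, acute phase proteins, IGF-1, the other blood markers, essential fatty acids, and the motor and language scores. Section 2.2 also makes the baseline biological profile and baseline development an objective in their own right. A value taken at two weeks would follow not only the product but also the care given at inclusion (deworming, malaria treatment after a positive test, and vitamin A where due; section 3.1.3). By its own wording, the development rule selects children who are ill, tired or irritable.

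A separate question is eligibility. If the venous draw fails, the scheduled haemoglobin reading fails with it, and nothing requires another reading before allocation.

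**Working it through.** **1. The plan's own figure.** Section 3.1.7 uses n = 16 s²/d². With d = 0.4 SD, 16/0.4² = 100 per cell. Allowing for 25% loss, 100/0.75 = 133.3, rounded up to 134, and 12 × 134 = 1608. This reproduces. Power at n = 100 is 80.7% (two-sided 5%). The point does not depend on this calculation, which concerns lean mass.

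**2. Timing under the rules as written.**

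| Scheduled time | Next scheduled visit | Status of a postponed value |
|---|---|---|
| Baseline | 2 weeks into supplementation | On product, unless the start is held back |
| Month 3 | Month 4 | About 1 month off product |
| Month 6 | None | No date given |

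A row of Table 2 labelled as fortnightly runs on to month 6. Even on that reading, a postponed 3-month value is off product. Under the monthly schedule, the fortnightly visit to which the development test is deferred does not exist after month 3.

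**3. Shares of exposure.** Three months is about 12–13 weeks. A baseline taken at 2 weeks lies 2/13 = 15% to 2/12 = 17% of the way into supplementation. A 3-month value at month 4 follows an off-product interval of 1/3 = 33% of the intervention's length.

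**4. Average dilution from late baselines.** Let f be the share of children with a late baseline. The documents give no figure, so f is assumed. If the effect builds up linearly, the average change-score effect falls by f × 2/W, where W is 12 or 13 weeks. Power is for a true 0.4 SD effect with 100 per group, borrowed from section 3.1.7 as an illustration.

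| Assumed f | Children of 1608 | Reduction in effect | Power |
|---|---|---|---|
| 2% | 32 | 0.3% | 80.5% |
| 5% | 80 | 0.8% | 80.1% |
| 10% | 161 | 1.5–1.7% | 79.4–79.5% |
| 30% | 482 | 4.6–5.0% | 76.6–77.0% |

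At f = 15%, the reduction is 0.15 × 2/13 = 2.3% to 0.15 × 2/12 = 2.5% (about 241 children).

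**5. Late 3-month values.** The corresponding loss is the share affected times the fraction of the effect that fades in the off-product month. The documents give neither quantity, so I put no figure on it.

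**6. Haemoglobin.** The measured route goes through the venous draw. The Table 2 footnote gives a second route, but at discretion and not tied to a failed draw. Clinical signs of decompensated anaemia give a third. A reading before allocation is therefore possible but not required.

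**The case against.** The strongest case against is that this is a small clarification. Section 3.1.9 already puts baseline data before the supplement, and no section says that a late value is to be analysed as baseline. If that order is kept, a baseline failure precedes the product and should be balanced across arms, leaving only slight dilution. The two-try limit appears under risks and benefits, where it protects children from repeated needling. Operational detail may sit in annex 6 or the data management plan, neither of which is in the text reviewed. Most of this stands, and it limits the size of the point.

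It does not remove the point. The 3-month problem arises however section 3.1.9 is read, and failures at month 3 occur after exposure, so balance across arms cannot be assumed there. The conflict is between rules written in the protocol itself. Nor is any extra attempt needed: a repeat is already planned, and only its date is at issue.

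Three stronger readings are tempting and unsupported:

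- A reader might infer that the haemoglobin exclusion cannot be checked before randomisation. The Table 2 footnote, the clinical-sign criterion and the requirement to complete screening before opening the envelope all say otherwise.
- A reader might infer that the trial's baseline is generally post-treatment. Only children with a failed draw or test are concerned.
- A reader might infer bias through adjustment for a contaminated baseline. Section 3.1.13 states baseline adjustment only for lean body mass, so for these secondary outcomes that would be an assumption about the model. A change score would nevertheless be diluted, as computed above.

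**Conclusion.** The concern holds within limits. The written rules would place some secondary-outcome values on product when labelled baseline, or off product when labelled month 3. They conflict with section 3.1.9 and offer no date after month 6. Only children with a failed draw or test are affected, and their share is unknown.

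The primary outcome, lean mass from deuterium dilution in saliva, needs neither assessment and is unaffected. The average dilution from late baselines is likely small: about 1–2.5% at an assumed 5–15% failure with linear build-up. That range excludes late 3-month values and would not describe a marker that responds early. For haemoglobin, the supportable statement is that after a failed draw the <4 g/dl limit might not be checked by measurement, because no independent reading is required.

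**What to change.** - Reconcile sections 3.1.9, 3.1.11 and 4.3 on whether baseline assessments must precede supplementation. Which order applies is for the investigators to settle.
- State that the existing haemoglobin criterion is resolved before the envelope is opened, as section 3.1.8 implies, using the HemoCue route in the Table 2 footnote if the venous draw fails.
- Replace postponement to the next visit with a repeat attempt within the one-week tolerance that section 3.1.10 already uses for visits, at each time point. Section 3.1.1 makes this practicable: "Admission and follow-up take place 5 days a week on each site".
- Record the actual date of every sample and test. In the main secondary analyses, do not treat a value taken after the first ration as baseline, or a value outside the window as month 3 or month 6. A sensitivity analysis may include them.

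The cost is a few sentences of wording, a short extra visit for the children affected, and slightly more missing values. The sample size and primary analysis do not change.
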